### Randomization and blinding

We will randomize participants based on a stratified randomization scheme using a permuted block method with a random number generator, in fixed random sizes. We will use an R30 or X100 with a cool A/P B70-type coil (Magventure Inc.) to ensure blinding of both patient and technician. As such, the clinician, researcher, patient and technician will all be blinded. For both active and sham stimulation, the coil is positioned under MRI guidance using real-time neuronavigation, thus providing technician and participant with visual feedback throughout stimulation.

### TBS treatment procedure

TBS will be delivered to the DLPFC bilaterally, with neuronavigation determined through structural MRI. The structural MRI utilized to derive the brain target will have been completed as part of P2. The coil position selection will start by identifying MNI152 stereotaxic coordinates (x, y, z) of (–38, +44, +26) and (26, 38, 44) in the left and right DLPFC, respectively, which we have shown to be effective targets for rTMS in alleviating symptoms of MDD (162). Bilateral TBS will be delivered as follows: R-DLPFC cTBS: 40s uninterrupted bursts (triplet 50 Hz bursts, repeated at 5 Hz, 40s on, 600 pulses total) followed immediately by L-DLPFC iTBS: (triplet 50 Hz bursts, repeated at 5 Hz, 2s on and 8s off, 600 pulses total). For intensity of stimulation we will use 120% RMT. Our work in over 200 people stimulating PFC suggests that 120% RMT is the maximum that should be used for negligible risk of seizure and other serious adverse effects beyond the expected scalp pain and headache during early treatment sessions (163, 164).

### Participants

Patients will be included if they meet general inclusion criteria for CDiA and in addition, if they:

(1) have a DSM–5 diagnosis of AUD based on the Mini-International Neuropsychiatric Interview (MINI (165) (2) do not exhibit problematic use of any substances (excluding nicotine and caffeine), including alcohol, for >1 month; (3) screened positive for an MDE based on the MINI without psychotic symptoms (4) are agreeable to keeping their current antidepressant medications and medications for AUD constant during the study; (5) are reliably taking SUD agonist therapies if appropriate and managed by their clinical team; (6) are able to adhere to the study schedule (7) meet the TMS safety criteria (166).

Participants are excluded if they meet general exclusion criteria for CDiA, and in addition, if they: (1) have a concomitant major unstable medical illness or any significant neurological disorder; (2) are pregnant or intend to get pregnant during the study; (3) have failed a course of ECT, due to the lower likelihood of response to rTMS; (4) have an intracranial implant (e.g., aneurysm clips, shunts, cochlear implants) or any other metal object within or near the head, excluding the mouth, that cannot be safely removed; (5) require a benzodiazepine with a dose equivalent to lorazepam 2 mg/day or higher (167).

Participants will be discontinued from the study if they cannot safely continue the study based on any of the following criteria: (1) experience clinically significant worsening of suicidality that requires an involuntary inpatient hospitalization; (2) develop clinically significant hypomanic or manic symptoms; (3) relapse into problematic substance use in the month prior to rTMS treatment or during the rTMS treatment; (4) miss four rTMS treatments (i.e., 20%); or (5) withdraw consent.

If relapse into substance use is suspected during rTMS treatment, for safety purposes (e.g., to manage seizure risk), a physician will be called to assess the participant prior to the initiation of rTMS treatment for the day or as soon as substance use is suspected. Investigations (e.g., urine drug screen or blood draw) will be ordered at the physician’s discretion, with the consent of the participant. The decision to continue with or discontinue rTMS treatment for that day or going forward will be at the discretion of the assessing physician and the participant’s SUD clinical team.

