### Objectives

The primary objective of P4 is to conduct a double-blind randomized pilot study, consisting of two arms (bilateral TBS and sham) to investigate the effect of bilateral TBS on deficits in EF in the context of comorbid AUD and MDD. We will also measure alterations in TMS-EEG-indexed GABA receptor mediated inhibition and DLPFC TGC as potential mechanisms mediating therapeutic effects. We will also assess the direct associations between improvement in EF domains after bilateral TBS, with improvement in MDD symptoms.

P4 will test six interrelated hypotheses (H1-H6). Specifically, we hypothesize that, compared with sham TBS, 4 weeks of daily bilateral DLPFC TBS will lead to:

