#### H2

Greater proportion of individuals remaining abstinent from substance use;

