### Methods and planned analyses

A total of 40 participants will be recruited from the CDiA pooled sample within 6 to 12 weeks of the baseline assessment for P1. Participants will be randomized in a 1:1 ratio to one of two different rTMS arms. The first arm will include bilateral TBS, applied as cTBS over the right DLPFC followed by iTBS applied over the left DLPFC. The second arm will be sham TBS. All participants will be asked to participate in 4 weeks of treatment, 5 days/week (i.e. weekdays). TMS-EEG will occur at treatment initiation (week 0) and treatment end (week 4). Baseline and post-treatment clinical measures will be administered to characterize each AUD patient. TBS will be administered using the MagPro X100 stimulator equipped with a Cool-B70 coil and Qooler fluid-cooling device (MagVenture, Farum, Denmark) positioned under MRI guidance using the Brainsight neuronavigation system. With a sample size of 20 participants per group and assumed large effect sizes, we will have 80% of statistical power to detect a significant difference between the active treatment arm and sham at a significance level of 0.05.

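### Project 4's stopping rule ends study participation rather than rTMS, so participants removed for relapse during rTMS or for four missed sessions would lose the only post-treatment EF test

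*Protocol article*

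**What the plan says.** The primary objective of Project 4 (Objectives) is to "investigate the effect of bilateral TBS on deficits in EF in the context of comorbid AUD and MDD". Project 4, Methods and planned analyses, sets 4 weeks of weekday treatment in two arms, randomized 1:1. Project 4, Clinical assessments, has the EF tasks repeated in the week before rTMS starts and again when the 4-week course ends. HRSD-17 and C-SSRS are also taken weekly; the EF tasks are not.

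The stopping rule is in Project 4, Participants: "Participants will be discontinued from the study if they cannot safely continue the study based on any of the following criteria". Five criteria follow. Two concern this point:

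- Criterion 3: "relapse into problematic substance use in the month prior to rTMS treatment or during the rTMS treatment".
- Criterion 4: four missed rTMS sessions, given as 20% of the course.

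The next paragraph covers suspected relapse during treatment and uses a narrower term: "The decision to continue with or discontinue rTMS treatment for that day or going forward will be at the discretion of the assessing physician". That decision is shared with the clinical team treating the participant.

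H2 of Project 4 predicts, for active stimulation, "Greater proportion of individuals remaining abstinent from substance use".

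**The concern.** Stopping stimulation and leaving the study are different events. Someone whose stimulation stops can still sit the EF tasks, which deliver none. The criteria list uses the broader term. If sites follow it literally, participants who relapse during rTMS or miss four sessions are gone before the single post-treatment EF measurement.

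Two things are at stake. One is precision: with 20 per arm, each lost value counts. The other is the randomized comparison: both events occur after randomization, and H2 itself expects substance use to differ between arms, so those left to analyse need not be comparable. An analysis plan can model missing values but cannot restore EF scores that were never collected.

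**Working it through.** **1. Where else could an EF value come from?** Table 1 lists the Flanker, N-back and Switch tasks at baseline and year end only; the bimonthly follow-ups have none. Project 4 participants are "recruited from the CDiA pooled sample within 6 to 12 weeks of the baseline assessment for P1". If rTMS starts at recruitment (an assumption), the course ends at weeks 6 + 4 = 10 to 12 + 4 = 16. Year end is month 12 plus or minus 1 month (Table 1, footnote c), about weeks 48 to 56. The gap is 48 - 16 = 32 to 56 - 10 = 46 weeks, too long to stand in for week 4. The 2-back task recorded with EEG covers updating only and belongs to the TMS-EEG session, which a participant out of the study would also miss.

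**2. The plan's power figure.** The basis is "With a sample size of 20 participants per group and assumed large effect sizes", 80% power and a significance level of 0.05. No effect size or sidedness is given. For a two-sample t-test the noncentrality is d × √(n/2), with 2n - 2 degrees of freedom. At n = 20:

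- d = 0.8, one-sided: 0.8 × √10 = 2.53, power 79.9%.
- d = 0.8, two-sided: power 69.3%.
- Two-sided 80% power needs d = 0.909 (0.909 × √10 = 2.87).

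The 80% is therefore reachable in two ways, and both are carried forward.

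**3. Power after assumed losses.** The document gives no loss rate; 10% and 20% are assumptions.

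| EF values per arm | d = 0.8, one-sided | d = 0.91, two-sided |
|---|---|---|
| 20 | 79.9% | 80.1% |
| 18 (10% lost) | 76.0% | 75.6% |
| 16 (20% lost) | 71.4% | 70.2% |

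**4. How many might reach criterion 4?** The course has 4 × 5 = 20 sessions, and 4/20 = 20%, as stated. With an assumed chance q of missing each session and independent misses, the number missed is Binomial(20, q). The chance of four or more is:

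- q = 5%: 1.6% (0.6 of 40 participants)
- q = 10%: 13.3% (5.3 of 40)
- q = 15%: 35.2% (14.1 of 40)

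These are not upper bounds. If misses cluster within people (beta-binomial, assumed intraclass correlation 0.1), q = 5% gives 8.3% and q = 10% gives 20.6%. In the other direction, removal also requires that the person cannot safely continue.

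**5. Can the direction of any bias be fixed?** Take a true difference of 0.80 SD and an assumed correlation ρ between EF change and staying in. In a latent-threshold model, the mean among those retained shifts by ρ × φ(z_p)/(1 - p), where p is the share removed. With 10% removed from active and 20% from sham:

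- ρ = 0.3: 0.800 + 0.058 - 0.105 = 0.754 (rounded from unrounded terms)
- ρ = 0.5: 0.800 + 0.097 - 0.175 = 0.723 (likewise)

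Reversing the rates gives 0.846 and 0.877; equal rates give 0.800. The sign depends on which arm loses more, which the document does not say. The shift of about 0.05 to 0.08 SD compares with a standard error of √(2/20) = 0.32 SD.

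**The case against.** The strongest reply is that the article condenses seven projects and its wording is mixed. Removal applies only to those who cannot safely continue. Suspected relapse goes to a physician who decides about rTMS alone, so the two paragraphs can be read together as a treatment-stopping rule, and few may leave for relapse. Eligibility requires more than a month without problematic use and an ability to keep to the schedule, which should limit both events. The full protocol may provide an early-termination assessment. This is a pilot, and interest in those who received the course is defensible for the mechanistic aims.

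Much of this stands, and it rules out several stronger readings that a reader might infer:

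- Relapse removes a participant automatically. The physician paragraph does not support that.
- No post-discontinuation visit exists. The article does not say so, and an unseen protocol may contain one.
- The EF estimate will be biased in a known direction. The document gives no rates by arm.
- The stated 80% power is wrong. It is reproduced under a standard calculation.

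The core remains. The list says participants leave the study, and nothing in the article provides for testing them afterwards. An attendance count is not in itself a safety event, and criterion 4 has no physician step. For relapse, two adjoining paragraphs use different terms for what stops, which is itself a reason to align them.

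**Conclusion.** The concern holds as a matter of stated wording. Read literally, relapse during rTMS (softened by physician discretion) and four missed sessions (not softened) cost the only post-treatment EF value for the primary objective. The loss follows a post-randomization event and, for relapse, overlaps with the abstinence outcome, though criterion 3 concerns problematic use rather than any use. It may therefore differ by arm.

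Size and direction cannot be derived from the document. The power figures of about 76% and 70-71% illustrate assumed losses of 10% and 20%; the attendance and bias figures also rest on assumed rates. Confidence is moderate because the full protocol is not at hand. This is a cheap improvement, not a flaw that invalidates the trial.

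**What to change.** Reword the criteria list so that relapse during rTMS and four missed sessions stop rTMS treatment only. Invite every randomized participant who started rTMS and has not withdrawn consent to the week-4 EF, HRSD-17 and C-SSRS assessments already scheduled. Apply the checks in Project 1, Measures: 12 hours without use and zero breath alcohol. Repeat TMS-EEG only if the physician agrees, given seizure risk after relapse. Leave criteria 1, 2 and 5, and relapse before rTMS, as they are. If the full protocol already provides such a visit, only this wording needs aligning.

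The cost is a wording change and an already planned visit for those who stop early. The downside is that some week-4 data will be off treatment, so the estimate becomes the effect of allocation to TBS rather than of completing it. Some who stop will decline or fail the checks, so recovery will be incomplete.

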### Clinical assessments

Participants will be initially screened with the MINI and C-SSRS. Interested and potentially eligible participants will complete a subsequent interview to address all criteria outlined above to confirm eligibility. The 17-item Hamilton Rating Scale for Depression (HRSD-17) (168) will be our tertiary clinical outcome measure. The tertiary clinical outcome criteria will be a decrease in HRSD-17 score at treatment end compared to baseline (150, 162). The HRSD-17 will be performed at baseline, weekly and at the end of the rTMS treatment course. The Columbia-Suicide Severity Rating Scale (C-SSRS) will be used to evaluate suicidality. This reliable and valid scale has been used in randomized clinical trials and is able to predict completed suicide (169). The C-SSRS has been reported as an effective measure for diagnosis and treatment across several diagnoses (170–172) with high internal consistency, and interrater reliability (172–176). The C-SSRS will be performed at baseline, weekly and at the end of the rTMS treatment course. TMS Adult Safety Screen (TASS) (166) will be used at recruitment and baseline to ensure that participants are safe to participate in rTMS treatment trials. To enhance integration with other projects, we will re-administer the EF cognitive assessments within one week prior to the start of rTMS and at the end of the 4-week course of rTMS.

### Neurophysiological indices of GABA receptor mediated inhibition in the DLPFC

To evaluate GABA receptor mediated inhibition indices in the DLPFC, TMS will be administered to the left DLPFC using two Magstim-200 stimulators (Magstim Company Ltd., UK) connected via a Bistim module and electrophysiological data will be collected using dedicated hardware and software (Neuroscan, Compumedics, USA). Each TMS session will include the establishment of the individual threshold for stimulation, followed by GABA receptor mediated inhibition paradigms in the DLPFC according to our published methods (160). Recordings will be acquired through a 64-channel EEG. GABA receptor mediated inhibition indices from the DLPFC will be the dependent variables of interest and derived according to published recommendations (160, 177). Our neurophysiological measures have been established in several of our previous reports and have a high test-retest reliability (i.e., ICC > than 0.9) (178, 179). Data analysis will take place using semi-automated methods developed and validated by our group (160, 178). TMS-EEG will be conducted prior to the start of the course of rTMS and within 48 hours after the last rTMS treatment.

To evaluate TGC, participants will undergo an N-back task (2-back condition) during a 10-minute EEG recording at baseline and after the treatment course as part of the TMS-EEG sessions. EEG signals of TGC are recorded using DC and a low pass filter of 100 Hz at 20-kHz sampling rate, and data processed offline using MATLAB and EEGLAB toolbox, following previously published protocols (180, 181). *Theta-Gamma Coupling*: The measure of TGC is indexed by the modulation index (MI), calculated for each electrode, followed by an average across the right and left frontal electrodes. The MI for all target trials is analyzed as a weighted average based on the number of correct and incorrect responses, as previously described (180, 181).

Finally, we will aggregate data from other CDiA projects (including imaging, genetics, inflammatory models, preclinical biomarkers and more) to further examine the role of GABA receptor mediated inhibition in the cognitive dysfunction found in SUD. Specific baseline cross-analyses will be performed between EF tasks, imaging variables, inflammatory markers and TMS-EEG indices of GABA receptor mediated inhibition.

## Project 5: a preclinical study of the effects of alcohol on EF and the impact of novel therapeutic interventions

### Background

Projects 1-3 will provide insight into the behavioral, neural and molecular underpinnings of EF deficits in SUDs. However, these studies are by design correlational, limiting our ability to establish causal relationships among putatively mechanistic factors. In contrast, P4 will test causal contributions of neuromodulation to EF improvement but is limited to a treatment modality with a demonstrated safety profile. In contrast, Project 5 (P5) will seek to causally establish specific molecular mechanisms and create a platform for testing novel pharmacological treatments targeting EF. To accomplish this, P5 will employ a reverse-translational approach using rats to examine EF-like deficits along the same three dimensions measured in P1-P4. To evaluate causal contributions to EF-like function, P5 will experimentally manipulate similar biological systems to those evaluated correlationally throughout the rest of the CDiA Program.

Preclinical research on substance administration has played a critical role in understanding the nature of substance-related cognitive dysfunction. However, studies have typically focused on single cognitive domains, and relatively little is known about the dynamic trajectories of executive dysfunction [i.e. emergence, dependence and potential reversal (182, 183)]. To address these gaps and complement the human studies in CDiA, P5 will measure in rats how EF-like performance in three domains is affected by chronic alcohol consumption (Objective 1), potential reversal via pharmacological intervention (Objective 2), and identification of peripheral and central biomarkers for translation to humans (Objective 3).

This investigation will target specific biological pathways implicated in EF deficits in AUD, and investigated correlationally across the rest of CDiA. Specifically, P5 will focus on GABAergic neurotransmission, the inflammasome system, the noradrenergic system, and the opioid system. The GABAergic system plays a critical role in cognitive functions (184), and will be investigated as a therapeutic mediator of neuromodulation treatment in P4. To complement findings from P4, P5 will enhance GABA activity pharmacologically during withdrawal in rats to investigate its impact on EFs. Similarly, the activity of the inflammasome, implicated in brain disorders (185) and alcohol consumption (186), will be measured in P3 for its translational biomarker value. To complement and extend P3’s correlational findings, P5 will block inflammasome activity pharmacologically (via MCC950), to assess its impact on EFs. The integrity of the noradrenergic system, to be measured through NM-MRI in P2, plays a critical modulatory role in AUDs (187), with complex effects depending on activity at various receptor subtypes (α1 versus α2). P5 will target the α2-noradrenergic receptor, using guanfacine, an α2-receptor agonist that demonstrated efficacy at reducing alcohol consumption in rats (188) and is used for the treatment of attention-deficit/hyperactivity disorder (189).

Finally, naltrexone is a prescribed medication used to manage alcohol dependence, especially consumption, although it appears to have reduced efficacy in certain patients, depending on gender and genetic differences (190). Naltrexone is predicted to be prescribed in a significant proportion of P1 participants. Its effects on EFs are not fully characterized and tend to vary from study to study (191, 192). Here, we propose to systematically investigate the relationship between its known clinical efficacy on consumption and potential improvement of EFs in rats, providing a clinically-relevant comparison to the other interventions.

### Objectives

The primary objective of Project 5 (P5) will be to characterize the impact of alcohol on three cognitive domains in rats, identify the impact of novel therapeutic approaches, and delineate novel biomarkers predictive of cognitive deficit emergence or treatment efficacy. We will test the following hypotheses:

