#### H2

Cognitive dysfunctions observed will be linked to changes in central biomarker of synaptic functions, changes in various neurotransmitter related activity and peripheral signs of neuroinflammation.

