### Methods and planned analyses

Male and female Long Evans rats, 3 months old at study initiation, will be utilized in this study. Rats will be habituated to consume a liquid diet (Nestlé^®^ Chocolate Protein Boost) in which ethanol can be diluted. After baseline assessment of EFs, half of each cohort will be exposed to a diet supplemented with 10% w/v alcohol 5 days per week. Removal on 2 consecutive days per week will induce a withdrawal period. Such cycle will be repeated 4 times, with assessment of cognitive functions during withdrawal after 4 cycles (**Figure 4**; top panel, orange box).

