Blood samples will be drawn weekly and 24 hours after discontinuation of the liquid diet (**Figure 4**) to verify 1) blood alcohol levels (BALs) exceeding 100mg% during exposure and 2) the absence of alcohol 24 hours after cessation when behavioral testing begins. BALs will be assessed using an ANALOX machine. Serum samples will also be utilized for measuring peripheral inflammasome biomarkers. Inflammasome activity will be determined by the phosphorylated/non-phosphorylated NALP3 ratio in peripheral blood mononuclear cells, along with investigating inflammatory markers (NF-KB, ERK, p38MAPK) and cytokines (IL-1β, IL-18, Caspase-1). Luminex xMAP technology^®^ will be employed for biomarker analyses.

After behavioral assessments, rats will be euthanized, and brains dissected for immunofluorescence staining and molecular analyses on regions of interest (prefrontal cortex, VTA, nucleus accumbens and hippocampus). Rostro-caudal coronal sections will be stored at -20°C for neuroinflammation, noradrenergic, and GABAergic marker analysis. RNA and proteins will be extracted from homogenized tissue, allowing for cDNA conversion, quantitative PCR, and Western Blot analyses. The markers examined include, but are not limited to, SST, PV, α5-GABRA, α1 GABRA, BDNF, and other GABAergic markers. Similarly, qPCR, immunostaining, and Western Blot analyses against sterile inflammation biomarkers (NALP3, NF-KB, ERK, p38MAPK, IL-1β, IL-18, Caspase-1) will validate the correlation of peripheral and central biomarkers in a region-specific manner. Investigation of changes in noradrenergic system markers (NET, α1 receptor, α2 receptor) will complement NM-MRI work outlined in P2.

The blood and brain samples collected will form a repository for subsequent biomarker analyses related to executive dysfunction in AUD. As Objective 3 establishes this repository, the analysis of these samples (peripheral or central) will be influenced by findings from other projects. Consequently, additional exploratory investigations of biomarkers will be conducted in these samples when other projects identify relevant pathways or markers in the clinical population.

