#### Proposed analyses

Behavioral data will be examined to assess the impact of alcohol exposure on EFs, utilizing ANOVA (or relevant non-parametric alternatives) followed by Tukey’s *post hoc* comparisons for statistical significance. In the alcohol-exposed groups, it is possible to observe subgroups of animals with higher susceptibility to alcohol than the others, suggesting existence of high-responders and low-responders.

For data collected weekly, data will be analyzed with repeated measures to identify animals that are more than 50% of the time over the mean, and animals that are more than 50% of the time under the mean to segregate high-responders and low-responders respectively. If such separation does not exist consistently, then analyses will focus on overall alcohol effect. For the second objective involving drug interactions, separate 2-way ANOVA with diet and treatment as factors will be applied, followed by Dunnett’s *post-hoc* comparisons (198). In Objective #3, blood sample data will be analyzed using Student’s t-test (Objective #1) or 2-way ANOVA (Objective #2) with diet and treatment as factors, followed by Dunnett’s *post-hoc* test. Brain analyses with qPCR and Western Blot will use 2-way ANOVA with diet and treatment as factors, followed by Dunnett’s *post-hoc* comparisons. Pearson or Spearman analyses will evaluate correlations between executive dysfunction and peripheral/central biomarker levels, with p-values adjusted for multiple comparisons using the Bonferroni method due to the potential high number of pairwise analyses.

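### Project 5 sets out to find biomarkers that predict deficit emergence or treatment efficacy, but its stated marker analyses test group effects and unordered association, not prediction

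*Protocol article*

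**What the plan says.** All places are in the Protocol article, Project 5.

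- **Objectives.** The third limb of the primary objective is to "delineate novel biomarkers predictive of cognitive deficit emergence or treatment efficacy".
- **Background.** The same objective is described more modestly, as "identification of peripheral and central biomarkers for translation to humans (Objective 3".
- **H2.** The hypothesis that covers markers is one of association: "Cognitive dysfunctions observed will be linked to changes in central biomarker of synaptic functions".
- **Methods and planned analyses.** After baseline EF assessment, "half of each cohort will be exposed to a diet supplemented with 10% w/v alcohol 5 days per week". EF is assessed again after four cycles.
- **Measures.** Dosing follows that assessment, with several doses tested in the same animal. "Blood samples will be drawn weekly and 24 hours after discontinuation of the liquid diet". The stated purpose is to check blood alcohol; serum is also to be used for inflammasome markers, but which draws will be assayed is not said. Brain tissue comes last: "After behavioral assessments, rats will be euthanized, and brains dissected". The Figure 4 legend agrees.
- **Proposed analyses.** Blood markers are analysed by t-test (Objective 1) or by two-way ANOVA on diet and treatment (Objective 2). For tissue, "Brain analyses with qPCR and Western Blot will use 2-way ANOVA with diet and treatment as factors". Finally, "Pearson or Spearman analyses will evaluate correlations between executive dysfunction and peripheral/central biomarker levels", with Bonferroni adjustment.

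**The concern.** To call a marker predictive of deficit emergence, its value must be measured before the deficit and must help tell which animals will develop it, beyond knowing which diet they received. To call it predictive of treatment efficacy, its value before dosing must tell which animals will gain from the drug. None of the stated marker analyses asks either question.

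What is at stake is the label that a marker carries out of the rat study. Project 5 is meant to supply markers for translation to humans. A marker that rises because a rat drinks alcohol, in a rat whose EF falls for the same reason, is a marker of exposure. If it were passed on as predictive, the human projects would spend effort on something that does not separate impaired from unimpaired exposed individuals. The efficacy half of the objective would have no direct test.

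**Working it through.** The article gives no power, alpha or effect size for this objective, so there is no figure of its own to reproduce. The check has two parts.

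**1. Objective against stated analyses**

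| Stated analysis | Role of the marker | Question answered | Tests prediction? |
|---|---|---|---|
| Blood: t-test, or two-way ANOVA (diet, treatment) | outcome | Does diet or drug change the marker? | No |
| Brain: two-way ANOVA (diet, treatment) | outcome | Does diet or drug change the marker? | No |
| Pearson or Spearman correlation with executive dysfunction | one of a pair | Do levels and dysfunction go together? | Only if the marker is measured earlier and diet is accounted for; neither is stated |
| High- and low-responder split of weekly data | no marker named | Are there consistent subgroups? | No |

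Timing settles the matter for brain markers: tissue is taken after behavioural assessments, so within one rat the marker cannot come before the deficit or the drug response. For serum the order is available (baseline EF, weekly blood during the cycles, EF after cycle 4, then dosing), but no analysis that uses it is stated.

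**2. What a pooled correlation can show when there is no individual-level link**

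Inputs from the article: a cohort of 48 rats (Figure 4 legend), half on the alcohol diet, with different animals for inhibition/working memory and for set-shifting.

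Assumptions:
- The two task groups are equal, so 48 / 2 task groups / 2 diets = 12 rats per diet. The alternative is 48 / 2 = 24 per diet.
- Diet shifts both marker and EF deficit by d within-group SDs.
- Marker and EF are unrelated within each diet group.
- The two diet groups are pooled. The article does not say whether they will be.

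With two equal groups, the pooled covariance is d²/4 and each pooled variance is 1 + d²/4. Hence

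r = (d²/4) / (1 + d²/4)

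- d = 1: 0.25 / 1.25 = 0.20
- d = 1.5: 0.5625 / 1.5625 = 0.36
- d = 2: 1 / 2 = 0.50

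Simulating normal data with d = 1.5 gives these proportions of studies with a significant pooled Pearson correlation:

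| Rats per diet | Unadjusted 0.05 | Bonferroni over 10 tests (0.05 / 10 = 0.005) |
|---|---|---|
| 12 | about 44% | about 13% |
| 24 | about 76% | about 41% |

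Repeat runs agree to within about one percentage point. The count of 10 tests is an assumption; the article gives none. Under the same assumptions, a test adjusted for diet rejects at its nominal level, because no within-diet link is left to find.

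**The case against.** The case on the other side has weight in several places.

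- **The hypotheses match the analyses.** H2 claims only a link and the Background only identification; ANOVA plus correlation tests that. On this view *predictive* is one loose word in a discovery-stage animal project whose further marker work is called exploratory. This stands, and it is why rewording is an acceptable repair. It does not remove the mismatch, because the strong wording sits in the primary objective.
- **Lag and covariates are details that a condensed article may leave to a fuller document.** Partly right. The text does not exclude correlating an earlier blood draw with later EF, and does not say that diet groups are pooled. A reader might infer both; the documents establish neither. The point is that the analyses the article does name answer a different question from the objective it states. No fuller analysis plan can place terminal brain tissue before the behaviour.
- **The planned correlation can find a real marker-EF link.** It can. For a true correlation of 0.6 in 24 rats, power is 0.888 unadjusted and 0.64 with Bonferroni over 10 tests. A reader might set the low power of a t-test for such a marker against a direct correlation and conclude that the plan would miss it; since that correlation is already planned, the comparison fails. Nor does any sentence say that a marker will be called predictive on a t-test or ANOVA alone.
- **Treated rats could enter the correlations.** True; the sentence is not restricted to untreated animals. It would still not show that the marker separates those who benefit from a drug from those who do not.
- **Weekly blood is not weekly marker data.** Correct. This bears on the cost of the fix.

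**Conclusion.** The concern holds as a mismatch between objective and analysis. As written, the marker analyses can support statements that a marker is changed by alcohol or drug, or is associated with executive dysfunction. They cannot support the statement that it predicts deficit emergence or treatment efficacy. For brain markers the limit lies in the design; for serum markers it lies only in the stated analysis.

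The size is conditional. If diet groups are pooled and diet shifts marker and EF by 1.5 SD each, a marker with no individual-level value correlates at 0.36 with EF. Bonferroni lowers how often this reaches significance but does not remove it, since it guards against chance and not against a shared cause. Smaller shifts give less (0.20 at 1 SD), larger ones more (0.50 at 2 SD). The mismatch itself does not depend on these figures.

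A reader might go further and infer that Project 5 cannot test prediction at all. The documents do not support that: blood is drawn during the alcohol cycles, before the post-cycle EF test and before dosing.

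**What to change.** For serum markers, state two tests and reserve *predictive* for markers that pass them:

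1. **Emergence.** Regress EF after cycle 4 on the marker from an earlier draw, with baseline EF and diet in the model.
2. **Efficacy.** Test the interaction between the pre-dosing marker and treatment on EF, with rat as a random effect because the same animal receives several doses.

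Report brain markers, and serum drawn at or after testing, as correlates. If the earlier draws will not be assayed for markers, reword the primary objective to say associated with, in line with H2.

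The cost is a change of wording and a few models, plus possibly extra assays on blood that is drawn anyway. Power for the interaction will be low, so some markers will have to be reported as undetermined for efficacy.
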